**Randomization, allocation and blinding**

If all eligibility criteria are met, and the presence of GTPS is determined, participants will be randomly assigned to receive 1) motor control exercises or 2) general exercises. Participants will be randomly allocated to two therapeutic arms using permuted block randomization to balance the number of patients allocated to each group. The randomization sequence of the permuted block (with six patients per block) will be generated by the website www.sealedenvelope.com. Participants will be informed of their random allocation by one of the researchers not involved in the evaluation process. After randomization, participants will be invited to return for physical therapy assessment, with a blind assessor, a physical therapist with 8 years of experience and a doctorate in the area of ​​musculoskeletal disorders. This evaluator will not participate in the screening or interventions. All participants will be advised not to disclose to the evaluator any details about the intervention program they have received (to ensure the allocation is hidden). In this evaluation, participants will give their free and informed consent.

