**Sample size and power analysis**

Sample calculation was performed using the G * Power software, based on the measure of the level of pain, as it is the primary outcome of the research. A power of 0.80, error probability α 0.05, effect size of 0.5 and dropout rate of 15% were used, for this we will recruit 60 participants (30 in each group)^9^.

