GTPS is, by definition, a painful syndrome, therefore, the specific cause of pain may be difficult to define, as more than one pathology can present similar symptoms in the hip region^5,6,17,19^. We will apply a combination of multiple clinical tests to avoid including participants who do not have GTPS, eg hip osteoarthritis^17,19^. The diagnosis of GTPS is clinical and two studies by Grimaldi et al. 2017 and Ganderton et al. 2017 demonstrated that palpation over the greater trochanter has a sensitivity of 80% and 85.7%, respectively, and a specificity of 47% and 61.1%, respectively. They also reported likelihood ratios of 0.43 and 2.2, respectively, demonstrating that this test alone, when negative, is able to rule out the presence of GTPS^6,19^. However, the combination of palpation and one of the other tests, FABER, Single leg stance for 30 seconds , FADER, FADER-R, ADD, ADD-R increases the chances of detecting GTPS due to the specificity of these tests, which can reach 100%^19^.

In order to maintain methodological quality, this clinical trial will comply with the standards of the consort group^30^. Study participants will be randomized to join one of the groups through the concealed allocation^17.30^. Due to the nature of the intervention, it is not possible to blind the clinician or participant to group allocation. Only the assessor of outcome measures and the statistician are able to be blinded to treatment allocation. The importance of not revealing anything to the assessor about the nature of the treatment will be strongly emphasized to participants. Statistical analysis will be conducted blind to treatment group allocation - actual groups will only be revealed after analysis. In addition, intention-to-treat analysis will be used, which preserves the study's randomization and simulates the real-life situation^31^. As a limitation of the study, we highlight the participation of women only, so care must be taken when extrapolating data to men with the same conditions.

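### A single stated block size of six, with unblinded clinicians and no stated separation of enrolment from past allocations, leaves on average a quarter of assignments deducible to anyone who tracks the sequence

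*Protocol*

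**What the plan says.** In the protocol section Randomization, allocation and blinding, the method is described thus: "Participants will be randomly allocated to two therapeutic arms using permuted block randomization to balance the number of patients allocated to each group". The block size follows: "The randomization sequence of the permuted block (with six patients per block) will be generated by the website". No variation of block size and no stratification are mentioned. Under Sample size and power analysis, the target is "for this we will recruit 60 participants (30 in each group").

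On blinding, the Discussion states: "Due to the nature of the intervention, it is not possible to blind the clinician or participant to group allocation". It also asserts concealment, "Study participants will be randomized to join one of the groups through the concealed allocation", without describing how this is done.

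Two sentences in the randomization section separate roles. The blind outcome assessor is kept apart: "This evaluator will not participate in the screening or interventions". Disclosure is handled as follows: "Participants will be informed of their random allocation by one of the researchers not involved in the evaluation process". Nothing separates the people who recruit, screen and enrol from the people who treat or otherwise know earlier assignments.

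**The concern.** Permuted blocks of one known size force the last places of each block. Hiding the future list does not help against this, because the prediction is made from past allocations, and in an open exercise trial these are visible to those who deliver the sessions. If such a person also has a say in who enters or when, the next arm can be known, or guessed better than by chance, at the moment of decision.

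Some room for influence exists. Entry depends partly on pain reported in provocation tests and on a determination that the syndrome is present, and the timing of entry can be moved. The Introduction also states an expectation that the motor control arm will do better. At stake is selection bias: arms that differ in prognosis at entry. Adjusting for the baseline value of the outcome would correct this only in part.

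**Working it through.** The protocol gives no predictability figure, so there is none to reproduce.

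**Inputs**
- Block size 6, fixed (Randomization, allocation and blinding).
- 60 women, 30 per group (Sample size and power analysis). A 3:3 split within blocks is inferred from the equal groups and the stated aim of balance. This gives 60 / 6 = 10 complete blocks.
- The total of 60 is taken as planned. The percentages below do not depend on it.

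**Certain allocations, fixed block of six**

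There are C(6,3) = 20 equally likely blocks. An allocation is certain once one arm has used its three places.
- 12 blocks have one certain allocation, 6 have two and 2 have three.
- Mean = (12×1 + 6×2 + 2×3) / 20 = 30 / 20 = 1.5 per block. The closed form 2m/(m+1) with m = 3 gives 6/4 = 1.5.
- Share = 1.5 / 6 = 25%. Over ten blocks, 10 × 1.5 = 15 of 60 are expected.
- By place in the block: 0% for places 1 to 3, 10% for place 4 (2/20), 40% for place 5 (8/20) and 100% for place 6. The sum is 0.1 + 0.4 + 1 = 1.5, as above.

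The figure is an average. A single block yields 1 to 3 certain allocations.

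**Best guess, fixed block of six**

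The strategy is to guess the arm with fewer allocations so far, and to toss a coin when they are level. Expected correct guesses per block of 2m are m + (2^(2m)/C(2m,m) − 1)/2. With m = 3: 3 + (64/20 − 1)/2 = 4.1 of 6 = 68.3%, against 50% by chance.

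**Effect of varying the block size**

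An observer who knows the possible sizes but not their order was simulated over 2,000 trials of 60, with sizes equally likely.

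| Scheme | Certain allocations | Best guess correct |
|---|---|---|
| Fixed 6 (exact) | 25.0% (15 of 60) | 68.3% |
| Random 4, 6 | about 5% (about 3 of 60) | about 69% |
| Random 4, 6, 8 | about 2% (1 to 2 of 60) | about 68% |

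The last column barely moves because every completed block is balanced, so the running totals alone show which arm is behind. The formula confirms it: expected correct guesses are 2.83 of 4, 4.10 of 6 and 5.33 of 8, and 12.26 / 18 = 68.1%.

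A larger fixed block would help less with certainty: fixed 8 leaves 20.0% certain and fixed 10 leaves 16.7%.

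**The case against.** A reader might infer that a quarter of allocations will in fact be known to the staff who enrol. The protocol does not support that. The 25% applies only to someone who influences entry, knows the ordered past allocations and knows where blocks start. The protocol does not say how many therapists there are, whether they share cases, or whether they see the order of enrolment.

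A reader might also infer that the concealment claimed in the Discussion fails. That is not shown either. Predictability can weaken concealment without defeating it, and the arrangements for holding and releasing the list may stand in a document not at hand.

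Two safeguards deserve weight. The person who discloses the allocation is outside the evaluation process. Because the section Physiotherapeutic evaluation counts the in-person eligibility screen as the first of two assessments, this can be read as excluding the screener too. The wording is ambiguous, and even on that reading it does not keep the screener from knowing earlier allocations. In addition, eligibility rests largely on explicit thresholds, and assignment follows once they are met. This narrows discretion but leaves some over borderline cases and timing.

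The mixed model adjusts for the baseline value of the outcome. That offsets selection on baseline pain in part, but not selection on unmeasured prognosis.

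Finally, self-report of pain by unblinded women is a different source of bias. Block size does not affect it, and it adds nothing to this point.

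**Conclusion.** The point holds in conditional form. The protocol commits to one stated block size in an open-label setting and does not separate enrolment from knowledge of past allocations. For a person placed to exploit this, on average 1.5 of 6 assignments (25%, about 15 of 60) are certain, and best guesses succeed 68.3% of the time. This rests on 3:3 blocks, and on that person knowing the sequence and, for certainty, the block boundaries.

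No effect on the pain comparison has been estimated, and predictability is not itself bias. The exposure is avoidable at almost no cost, and following the protocol as written leaves it in place. It should be changed.

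**What to change.** In the section Randomization, allocation and blinding:

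1. State that those who recruit, screen and enrol have no access to earlier allocations. Have an existing team member who does not recruit, screen or treat hold the list and release one assignment at a time, only after consent and baseline assessment are complete. The section now places the blind assessor's visit and consent after randomization, so the order of steps must change for this.
2. Replace the fixed block of six with randomly varied sizes, for example 4, 6 and 8.
3. Keep the sizes out of any document seen by recruiting, screening or treating staff.

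Step 2 removes most of the certain allocations (25% to about 2%) but leaves best-guess success near 68%. Step 1 is therefore needed too and should not be treated as optional.

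The cost is regenerating the list, assigning roles within the existing team and reordering the entry steps. If the last block is incomplete, the final imbalance is at most four women (half of the largest block, 8 / 2).

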**Physiotherapeutic evaluation**

Potential participants who meet the eligibility criteria over the phone will undergo two assessments. The first will be held to screen for inclusion and exclusion criteria that were not possible to assess by phone, as well as explain in more detail the nature of the study and the commitment required, with an opportunity for participants to ask questions, and the second will be carried out by a blind evaluator to assess outcomes. The physical therapy evaluation will be carried out at São Paulo State University and will take about 40 minutes to 1 hour. The assessment will be done by a physical therapist with 8 years of experience, with a master's degree in the area of ​​musculoskeletal disorders. Demographic data will be collected, including age, weight, height, BMI, etc. It will be determined whether the participants have the ability to manipulate shoes and socks^18^, have limited range of motion of the spine, hips or lower limbs that affect gait or data collection, or a visible discrepancy in the lower limbs. It will be evaluated whether the participants have sensitivity to palpation over the greater trochanter region of the femur^8,19,20^. If both hips are symptomatic, the more painful side will be evaluated ^10^. The Trendelenburg sign, which is the pelvic drop during unipodal support, indicating inefficiency of the hip abductor muscles, will be evaluated^5,8,19^.

The tests that will be used for clinical evaluation aim to define the exact location of the pain and transmit compressive and/or tension forces in the tendons of the hip abductor muscles on the greater trochanter. Participants must experience pain over the greater trochanter of the femur in ≥ two of the seven provocative clinical trials for pain^12,14,17^. They are:

• Greater trochanter palpation: positive palpation sensitivity, considered when there is pain over the greater trochanter of the femur, during assessment in lateral decubitus (LD) with the pain side up, flexion of the hip joint and knees together^5,6,8.11.17^. This test has been reported to have a sensitivity of 85.7% and a specificity of 61.1%^6^.

• FADER: Participants in dorsal decubitus (DD) should report pain over the greater trochanter when the affected lower limb is positioned in 90º flexion, adduction and external rotation of the hip^17^.

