**Statistical analysis**

The study will be run as a superiority trial. The statistical analysis will follow the intention-to-treat concept. Statistical analysis will be performed using the software IBM SPSS Statistics for Windows, version 20.0 (IBM Corp., Armonk, N.Y., USA) and statistician will be blind. Data will be evaluated using exploratory statistical techniques. Firstly, the normality and homogeneity of the data will be verified and then the appropriate statistical analyses will be adopted for the variables. The between-group differences and their respective confidence intervals at 95% will be calculated by constructing mixed linear models interaction of group data versus time. The linear mixed-effect model will be applied to the primary and secondary outcomes. “Time” and “group” will be considered fixed effects, whereas the participants will be considered random effect. The dependent variable baseline values will be included as a covariate for the correction of possible baseline between-group differences.

A causal mediation analysis will be conducted using the “mediate” package in R (The R Foundation for Statistical Computing). A model-based inference approach will be used to estimate the average causal mediation effect (ACME), average direct effect (ADE) and the average total effect^29^.

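### As written, baseline outcomes come after randomisation, and apparently after women learn their arm, so the baseline covariate can carry an allocation effect

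*Protocol*

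**What the plan says.** All references are to the protocol.

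- **Physiotherapeutic evaluation** describes two assessments. Of the first: "The first will be held to screen for inclusion and exclusion criteria that were not possible to assess by phone". It also serves to explain the study. Of the other: "the second will be carried out by a blind evaluator to assess outcomes".
- **Randomization, allocation and blinding** sets the trigger for randomisation: "If all eligibility criteria are met, and the presence of GTPS is determined, participants will be randomly assigned". It then says: "Participants will be informed of their random allocation by one of the researchers not involved in the evaluation process". After that comes: "After randomization, participants will be invited to return for physical therapy assessment, with a blind assessor". Of the same visit it adds: "In this evaluation, participants will give their free and informed consent".
- **Discussion** accepts that "it is not possible to blind the clinician or participant to group allocation".
- **Primary outcome** has the participant herself mark current pain and her average pain over the past week on a 100 mm line, at baseline and at 8 weeks.
- **Statistical analysis** specifies a linear mixed model and says: "The dependent variable baseline values will be included as a covariate". The stated purpose is to correct baseline differences between the groups.

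**The concern.** Adjusting for a baseline value is safe when allocation cannot have influenced that value. Measuring it before randomisation guarantees this. Here the only pre-treatment outcome assessment follows randomisation, and women may already know their arm when they mark the scale. Blinding the assessor does not protect a line that an unblinded participant draws herself.

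Two things are at stake. First, the primary comparison: if knowing the arm changes reported baseline pain differently in the two groups, the adjustment moves that difference into the treatment estimate. Second, the intention-to-treat set: a woman can be randomised and then decline or not return, leaving neither consent nor a baseline value.

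**Working it through.** **Step 1: order of events.** Set side by side, the two sections give: eligibility screening, randomisation on eligibility alone, allocation made known, return visit with the blind assessor for consent and outcome assessment, then treatment. I found no outcome measurement placed before randomisation.

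**Step 2: is the return visit the baseline visit?** Consent is given there, and first consent cannot follow 16 treatment sessions. So it is not the 8-week visit. It matches the second assessment in the section on physiotherapeutic evaluation.

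**Step 3: is the arm known by then?** The disclosure sentence stands between randomisation and the return visit, but no date or visit is attached to it. Participants are told not to reveal their programme to the evaluator, but that instruction speaks of a programme already received and fits follow-up visits too. Baseline after randomisation is explicit; disclosure before baseline is an inference.

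**Step 4: which baselines are exposed?** The VAS, catastrophizing, kinesiophobia, central sensitization and hip function scores are self-reported. Isometric strength depends on effort. Global perceived effect is not exposed, because it has no baseline.

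**Step 5: effect on the adjusted difference.** The protocol has no figure of its own to reproduce here: it gives no SD, no baseline-to-follow-up slope and no expected shift. Let β be the within-arm slope of 8-week pain on baseline pain, and b the difference between arms in reported baseline caused by knowing the arm.

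Adjusted difference = (difference in 8-week means) − β × (difference in baseline means)

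If the shift affects baseline only, bias = −β × b. If it persists in full to 8 weeks, bias = b − β × b.

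Assumed values: β from 0.3 to 0.7, b from 0 to 10 mm. Each cell shows the bias for a baseline-only shift, then the two-sided type I error simulated with SD 20 mm (assumed), 30 women per arm, true effect zero and 4,000 runs.

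| b (mm) | β = 0.3 | β = 0.5 | β = 0.7 |
|---|---|---|---|
| 0 | 0; 5% | 0; 5% | 0; 5% |
| 2 | −0.6 mm; 5% | −1.0 mm; 6% | −1.4 mm; 6% |
| 5 | −1.5 mm; 6% | −2.5 mm; 9% | −3.5 mm; 14% |
| 10 | −3.0 mm; 9% | −5.0 mm; 18% | −7.0 mm; 43% |

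If the shift persists in full, β = 0.5 and b = 10 mm give 10 − 0.5 × 10 = +5 mm, the opposite sign.

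**The case against.** The strongest reply is that the harm rests on two unproven links: that women know their arm at the baseline visit, and that knowing it moves their reports differently by arm. Both arms are active and look alike: 8 weeks, two individual sessions a week, 16 sessions of 50 to 60 minutes, and the same elastic-band progression. Differential relief or disappointment is less likely than against no treatment. A shift common to both arms does no harm, and a 2 mm difference barely moves the type I error. This stands, and it limits what can be claimed.

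A reader might infer more than the documents support:

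- *That the primary comparison is biased.* It can be; nothing in the protocol shows that it is.
- *That the bias runs opposite to the baseline shift.* This holds only if the shift has gone by 8 weeks.
- *That the bias is a known share of the planned effect.* Slope, shift and SD are all assumed, and the effect size of 0.5 is given without its metric.
- *That the whole shift enters through change scores.* No change-score analysis is planned.
- *That women without a baseline are dropped from the model.* The protocol does not say how missing baselines are handled, and an SAP may.

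None of this answers the sequencing itself. The text puts consent and the only pre-treatment outcome assessment after randomisation, and it names no safeguard that keeps the arm from the participant until they are done.

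**Conclusion.** The point holds as a defect of sequence. On the protocol's wording, baseline outcomes follow randomisation, and probably disclosure, and they then serve as the covariate in the primary model. The adjusted 8-week difference can therefore be biased.

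Neither size nor sign can be found from the protocol. Under the assumed slopes and shifts, with the shift confined to baseline, the bias runs from 0 to 7 mm in absolute size (0 to 5 mm at slope 0.5). It is zero if knowing the arm does not move reported baseline differently between groups.

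The intention-to-treat set is weakened in either case, because randomisation precedes consent. If the arm is disclosed first, the decision to decline or stay away can also depend on it.

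**What to change.** Rewrite the section on randomization, allocation and blinding so that the order is: eligibility visit, consent, baseline of all outcomes by the blind assessor, randomisation, disclosure of the arm. State that the allocation is not released until the baseline form is complete. If baseline was in practice taken before randomisation, correct the section to say so, and bring the section on physiotherapeutic evaluation into line.

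The cost is wording and visit order: the same two visits, assessor and measures. It should be done before enrolment, since a covariate free of allocation cannot be recovered once baseline has been taken after disclosure.

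The change makes the baseline sound and keeps women who never consented out of the randomised set. It does not remove reporting bias at follow-up. Participants stay unblinded, and an allocation-driven shift in reported pain at 8 weeks would still enter the comparison.

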**Ethical approval and consent**

The study was approved by the Research Ethics Committee of the Faculty of Philosophy and Sciences, São Paulo State University (UNESP) , Campus of Marília (CAAE: 87372318.1.0000.5406). All participants will sign an informed consent form.

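### As written, consent is given only after the screening tests and randomisation, and the baseline assessment also follows randomisation, so the intention-to-treat comparison is exposed if women decline or fail to return by arm

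*Protocol*

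**What the plan says.** The order of events is set in the Protocol under *Randomization, allocation and blinding*. The trigger for randomisation is eligibility: "If all eligibility criteria are met, and the presence of GTPS is determined, participants will be randomly assigned to receive" one of the two programmes. Consent is not named as a condition. The section then says: "Participants will be informed of their random allocation by one of the researchers not involved in the evaluation process". Next comes the visit: "After randomization, participants will be invited to return for physical therapy assessment, with a blind assessor". It closes with: "In this evaluation, participants will give their free and informed consent".

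Two other sections bear on timing:

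- *Ethical approval and consent* says "All participants will sign an informed consent form", without saying when.
- *Physiotherapeutic evaluation* describes two assessments. The first checks the remaining eligibility criteria, "as well as explain in more detail the nature of the study and the commitment required", with room for questions. It mentions no signature. The second is the outcome assessment by the blind evaluator.

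On analysis, *Statistical analysis* says "The statistical analysis will follow the intention-to-treat concept" and enters the baseline value of each outcome as a covariate. The *Discussion* justifies intention-to-treat on the ground that it preserves the randomisation, and says that participants cannot be blinded to their group.

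**The concern.** There are two separate matters.

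The first is the consent sequence. As written, women attend a research screening examination, with up to seven tests meant to provoke pain, and are then randomised, all before consenting. This stands whether or not anyone later refuses.

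The second is statistical. The trial is open to participants, and the programmes are visibly different: one is specific to the hip, the other general exercise. A woman who knows her arm before she commits can let it influence whether she consents or comes back. If she does not, she has been randomised but contributes no consent, no baseline value and no outcome. The set that reaches the model is then the women who were randomised and afterwards consented and attended. If that later step depends on arm and relates to pain, the comparison is no longer the randomised one. The analysis cannot repair this, because the missing women have no data.

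**Working it through.** No figure in the Protocol bears on this point, so the main check is to set the sections side by side.

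**Order of events**

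| Step | Section | Timing given |
|---|---|---|
| Screening examination, provocation tests, study explained | *Physiotherapeutic evaluation* | First assessment; no consent mentioned |
| Random assignment | *Randomization, allocation and blinding* | Once eligibility is confirmed |
| Participant told her arm | same | Not stated; listed before the return visit |
| Assessment by the blind assessor | same | Stated to follow randomisation |
| Consent | same | At that assessment |
| Signed form required | *Ethical approval and consent* | None |

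The sentences between the return visit and the consent sentence concern that visit's assessor, so the evaluation at which consent is given is most naturally the return visit. That consent follows randomisation is therefore stated. That it follows disclosure of the arm is inferred from sentence order.

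The baseline outcome assessment is the same return visit. A woman lost between randomisation and that visit lacks a baseline value wherever consent is placed.

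**Illustration of size**

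The planned number per arm (30) and the effect size (0.5) come from *Sample size and power analysis*. The refusal counts and outcome differences are assumptions.

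- Overall loss at this step, assumed 5% to 15%: 60 × 0.05 = 3 women; 60 × 0.15 = 9 women.
- Suppose 4 of 30 refuse in one arm only, so f = 4/30 = 0.133.
  - If refusers differ from the whole arm's mean by 0.5 SD, the mean of those remaining shifts by f/(1 − f) × 0.5 = (4/26) × 0.5 = 0.154 × 0.5 = 0.077 SD.
  - If they differ from the consenters by 0.5 SD, the shift is f × 0.5 = 0.133 × 0.5 = 0.067 SD.
- Reading the planned effect size as a standardised difference, these are 0.077/0.5 = 15% and 0.067/0.5 = 13% of it.
- Other assumptions, with the difference measured against consenters: 10% refusing with 0.5 SD gives 0.10 × 0.5 = 0.05 SD (10% of 0.5); 20% refusing with 1.0 SD gives 0.20 × 1.0 = 0.20 SD (40% of 0.5).

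With no refusals, or with refusals unrelated to arm and outcome, the bias in the comparison is zero.

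**The case against.** The best case for the plan has four parts.

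1. **Disclosure may come later.** The section gives no time for telling women their arm, and it is not strictly chronological: how the sequence is generated comes after the statement that women are assigned. If the arm were disclosed after the return visit, refusal could not depend on knowing it. This stands as a limit. A reader might infer that the Protocol fixes disclosure before consent, but it does not say so outright. It does say that the consent visit follows randomisation.

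2. **The sentence may be misplaced drafting.** The first assessment already includes an explanation of the study and time for questions, which is usual consent content. The consent form is not part of the text reviewed and may state a time. This is plausible, but no section available places consent earlier. If practice differs from the text, the text still has to be corrected.

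3. **Moving consent alone does not secure the analysed set.** This is right. A woman who signs early, is randomised and then does not return would still have no baseline value, so the timing of the baseline assessment has to change as well.

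4. **The size is not established.** The refusal numbers and the SD differences are all assumed. The Protocol does not say on what scale its effect size of 0.5 is measured. Baseline adjustment could absorb part of a difference already present in baseline pain. All of this stands. How the analysis set is defined and how a missing baseline is handled may also properly be left to the statistical analysis plan, and no fault is found there.

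**Conclusion.** The point holds as a defect in the order of events. The Protocol places consent at a visit after randomisation, and nothing else in it corrects this. The screening tests and randomisation therefore precede consent as written, and that alone requires correction.

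The statistical consequence is conditional. A reader might conclude that the intention-to-treat set is already broken. The documents do not support that: harm arises only if women decline or fail to return, differently by arm and in a way related to pain, and no expected number is given. The shift of about 0.07 to 0.08 SD for 4 refusals among 30, and the wider span of 0.05 to 0.20 SD, show what a few losses could do in arms of this size. They are not estimates of what will happen.

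**What to change.** - Under *Physiotherapeutic evaluation*, state that written consent is obtained at the first face-to-face visit, before the provocation tests and before randomisation.
- Delete the consent sentence from *Randomization, allocation and blinding*, and give the same timing under *Ethical approval and consent* so that the three sections agree.
- Hold the planned blind baseline assessment before randomisation and before any woman is told her arm. Every randomised woman then has consent and a baseline value, and the baseline pain score, which is self-reported, cannot be coloured by knowledge of the arm.
- State when the allocation is disclosed.

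The cost is Protocol wording, an ethics notification and a reordering of visits that are already planned. No visit or staff is added. The change should be made before enrolment or, failing that, for all remaining enrolment, because women who never consented cannot be recovered in the analysis.
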